### Criteria for discontinuing or modifying allocated interventions {11b}

No discontinuation criteria or plans to modify allocated interventions have been outlined for this trial. However, should the Data Safety and Monitoring Board (DSMB) determine the risks of participation outweigh the benefits for specific or all participants, they can recommend termination of the trial. The Trial Steering Committee will consider the advice of the DSMB and will vote to make a final decision on whether these recommendations should be implemented.

### Strategies to improve adherence to interventions {11c}

Prior to initiating the trial, our adherence strategies include (1) providing extensive theoretical and practical training to master trainers, supervisors, and non-specialist facilitators and (2) assessing their fidelity levels with the Activity Completion Checklists (ACC) and competency levels with the WHO CST Adult–child Interaction Fidelity rating scale and the ENhancing Assessment of Common Therapeutic factors (ENACT) [23]. During the trial, we will maintain intervention adherence in the group sessions by ensuring continued supervision of non-specialist facilitators by CST supervisors. CST supervisors are specialists (in psychiatry in Ethiopia, in occupational therapy or clinical research nursing in Kenya) and received CST training directly from the WHO CST team. Just after the trial’s start, the competence of non-specialist facilitators leading home visits will be assessed using the WHO CST Adult–child Interaction Fidelity rating scale. Throughout the trial, the supervisors will observe three out of the nine group sessions, during which they will rate the facilitators’ competency and fidelity using the ENACT and ACC and record other session-related observations. CST supervisors will provide both individual and group feedback to the non-specialist facilitators about the CST intervention’s delivery. Facilitator and observer feedback forms, ACC, and ENACT data will be used as resources for supervision, including exploration of non-specialist facilitators’ experiences. Supervision record forms will be used to document the supervision. Monthly in-country and cross-country supervision coordination meetings will be held to ensure the CST intervention is implemented consistently across sites and to allow for discussion of common challenges observed across sites.

In Ethiopia, during home visits caregivers will be requested permission to record the facilitator interacting with the child. Through viewing these recordings and providing feedback based on these recordings, supervisors can support non-specialist facilitators in ensuring the CST goals set for the individual family align with the child’s developmental level and that the facilitator implements the CST strategies well with individual children. Security concerns preclude taking video recordings in Kenya. In the Kenyan sites, supervisors will join the facilitator to attend a subset of the home visits. Lastly, we define adherence to the CST intervention as the family participating in at least 7 group sessions and 2 home visits. We will monitor and promote adherence by organising CST group sessions in central, accessible locations, taking attendance at each group session, providing childcare support when caregivers attend sessions with their children, following up immediately with caregivers if group sessions or home visits are missed, and where necessary, by sending reminders before each scheduled activity.

### Relevant concomitant care permitted or prohibited during the trial {11d}

Families that previously participated in the CST intervention in Ethiopia and Kenya will be excluded from the trial (see exclusion criteria outlined above). Throughout the trial, caregivers will be encouraged to seek medical support or other locally available support (including any locally available education support), as needed. Our team has prepared site-specific resource kits for families to encourage help-seeking.

### Provisions for post-trial care {30}

Supports and resources specific to the trial, such as free child diagnostic assessments by clinical specialists and reimbursements for travel costs to health centres for project-related assessments, will be suspended after the trial ends. However, trained community support workers and health and education workers will retain the ability to identify, refer, and assess children suspected of having developmental disabilities. Caregivers will also receive site-specific resource lists with information about relevant local resources and services that will continue to provide care after the trial’s termination.

### Outcomes {12}

There are two co-primary outcomes: (1) the frequency of a child’s internalising and externalising problem behaviours measured using total raw scores of the preschool and school-age versions of the Child Behavior Checklist (CBCL) [24–27] and (2) the quality of life of the child’s family measured using total scores of the family impact module of the Pediatric Quality of Life (PEDsQL) measure—acute version, asking about the family’s quality of life across the past 7 days [28]. Both measures are caregiver-reported and will be assessed at T0 (baseline), endpoint (T1, 18 ± 2 weeks after randomisation), and follow-up (T2, 44 ± 2 weeks after randomisation). The primary time point of interest for the primary outcome variables is T1.

There are 12 secondary outcomes.

We have prioritised the PEDsQL and CBCL assessed at T2 as our most important secondary outcomes, to examine if any effects are sustained at follow-up. There are ten additional secondary outcomes which include:Caregivers’ experience of stigma measured with an adapted version of the family interview schedule [29], given the high rates of stigma and discrimination experienced by families of children with DDs in these contexts [10, 30].Caregivers’ internalisation of stigma related to their child’s condition using an adapted version of the affiliate stigma scale [31], given the tendency for caregivers to self-stigmatise based on their experiences with their child [32].Caregivers’ depressive symptoms using the Ethiopian validated version of the Patient Health Questionnaire (PHQ-9) [33, 34], given extant evidence on the link between stress among caregivers of children with DDs and depressive symptoms [35, 36].Caregivers’ knowledge and competencies relating to CST strategies using the WHO CST knowledge and skills checklist based on the perceived critical role of CST strategies in reducing child externalising and internalising problems [22].Caregivers’ quality of life with the EuroQol 5 Dimensions 5 Levels (EQ-5D-5L) [37].Children’s quality of life using a child proxy version of the EQ-5D-5L measure, referred to as the EuroQol 5 Dimensions Youth (EQ-5D-Y) [38]. To be used only in Kenya, because no validated version approved by the licence holder is available for use in Ethiopia.Caregiver’s perspective of the family’s access to food using the Household Food Insecurity Access Scale (HFIAS) [39], considering the evidence demonstrating that caregiving responsibilities often prevent caregivers from engaging in viable economic activities and lead to economic hardship [35, 40].Caregivers’ reported use of physical discipline on their child using the discipline section of UNICEF’s Multiple Indicator Cluster Survey (MICS) [41] based on reports from our pilot studies indicating reductions in caregivers’ use of physical punishment on their children with DDs [10].Caregivers’ reported level of social support using the Oslo Social Support Scale [42] based on reports of social isolation experienced by caregivers of children with DDs and the CST’s group discussion format that brings caregivers together and promotes engagement among families with similar characteristics and experiences [43].Caregivers’ report of their child’s mode and function of communication using an adapted version of the communication profile [44] based on the CST’s purported goal to increase communication and engagement in children with DDs [9].

All outcomes will be assessed at T0 (baseline), T1 (18 ± 2 weeks—in other words, around 18 × 7 = 126 days or ~ 4 months after randomisation), and T2 (44 ± 2 weeks—in other words, around 44 × 7 = 308 days or ~ 10 months after randomisation). Two of these additional outcomes, the EQ-5D-5L and the EQ-5D-Y, are only collected in the context of the health resource impact and cost and consequence analysis and will not be reported in the main trial paper. All other outcomes will be reported in the main trial paper. The main evaluations focus on the primary outcome measures at T1, the primary outcome measures at T2, and the secondary outcome measures at T1. Analyses of the remaining eight secondary outcome measures at T2 will be exploratory only and may or may not be reported in the main trial paper. The pre-specified exploratory moderation analyses will be reported in the main trial paper. The health resource impact and cost and consequence analysis and the mediation analyses will not be reported in the main trial paper.

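### Reporting of eight secondary outcomes at T2 is left optional with no criterion, which leaves room for selective reporting at the last randomised comparison

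*Protocol article*

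**What the plan says.** All statements below are from the protocol article, section Outcomes {12}, unless another place is named.

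- The total is stated as "There are 12 secondary outcomes". Two are the CBCL and PEDsQL at T2, which are given priority. For the rest, "There are ten additional secondary outcomes which include" the stigma, depression, knowledge, quality-of-life, food insecurity, discipline, social support and communication measures.
- The EQ-5D pair is set aside: "Two of these additional outcomes, the EQ-5D-5L and the EQ-5D-Y, are only collected in the context of the health resource impact and cost" work, and the pair stays out of the main paper.
- A general rule follows: "All other outcomes will be reported in the main trial paper".
- The eight scales that are left are then treated differently at T2: "Analyses of the remaining eight secondary outcome measures at T2 will be exploratory only and may or may not be reported in the main trial" publication.
- The next sentence fixes the reporting of a different exploratory set: "The pre-specified exploratory moderation analyses will be reported in the main trial paper".

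Appendix Table 2 schedules all of these scales at T0, T1 and T2. The section on statistical methods for primary and secondary outcomes {20a} fits the co-primaries with both post-randomisation readings in one model and an arm-by-time interaction. It applies similar models to the other secondary outcomes and extracts the T1 effect. The section on the choice of comparators {6b} offers the intervention to the control arm once T2 data collection is complete.

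**The concern.** Calling an analysis exploratory limits what may be claimed from it. It is not a reason to leave open whether the result appears. Here eight scales are measured at T2 in both arms, and the article leaves their place in the main paper open without saying what the choice depends on, when it is made, who makes it, or where the results go otherwise.

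At stake is an even-handed account of whether effects on stigma, depressive symptoms, discipline, social support, communication and the other scales persist from week 18 to week 44. The article treats persistence as important, since that is its reason for giving priority to the CBCL and PEDsQL at T2. Because the control arm is then offered the intervention, T2 is the last point at which the arms can be compared as randomised. If T2 results appeared only where they were favourable, readers of the main paper could not tell a sustained effect from a chance finding among eight.

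**Working it through.** **1. The count.** Inputs from Outcomes {12}: 12 secondary outcomes, of which 2 are the CBCL and PEDsQL at T2 and 2 are the EQ-5D measures.

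12 − 2 − 2 = 8.

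This reproduces the article's figure. The eight are experienced stigma, affiliate stigma, PHQ-9, CST knowledge and skills, HFIAS, MICS discipline, Oslo social support and the communication profile.

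**2. The reporting rules side by side.**

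| Analysis | Status | Main paper |
|---|---|---|
| CBCL, PEDsQL at T1 | co-primary | yes |
| CBCL, PEDsQL at T2 | main secondary | yes |
| Eight scales at T1 | secondary | yes |
| Moderation analyses | exploratory | yes |
| EQ-5D measures | economic analysis only | no |
| Mediation, health economics | separate | no |
| Eight scales at T2 | exploratory | optional |

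Only the last row has no fixed rule. Its exploratory label does not explain this, because the moderation analyses carry the same label and are committed.

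**3. When the estimates become available.** With T1 and T2 as joint dependent variables and an arm-by-time term, a single fit yields both effects. If the similar models for the eight scales keep that structure, the T2 effects exist as soon as the T1 effects do. A reporting choice not fixed beforehand can then be made with them in view.

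**4. Illustration of what chance alone can produce.** The article states an alpha only for the co-primaries (0.025 each) and none for secondary outcomes, so a two-sided 0.05 per scale is an assumption. With no true effect on any of the eight, and independence:

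- at least one nominally significant result in either direction: 1 − 0.95^8 = 0.337;
- at least one favouring the intervention: 1 − 0.975^8 = 0.183.

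The eight scales are likely to be positively correlated. The documents give no correlations, so a range was simulated (400,000 draws, equal correlation r, threshold 1.96):

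| r | Either direction | Favouring CST |
|---|---|---|
| 0 | 34% | 18% |
| 0.3 | 30% | 15% |
| 0.5 | 25% | 13% |
| 0.7 | 19% | 9% |

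These are familywise chances for any eight nulls. They show how much chance material a free choice would have to draw on. They do not estimate reporting bias in this trial.

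**The case against.** Several points on the other side are fair.

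- **Timing of the choice.** A reader might infer that the decision will be taken after the results are known. The article does not say so. It promises a detailed SAP approved by the DSMB, and the trial statistician stays masked until the SAP is signed. That document is not shown and could settle the matter in advance. So the concern is conditional.
- **Place of publication.** The article uses the main paper to divide analyses between publications. Leaving a result out of it does not mean that the result is never published. This stands, although for these eight no other outlet is named.
- **Selection scale by scale.** The sentence treats the eight as one group. Showing one and omitting seven is allowed by the wording, but it is not a stated intention.
- **The general rule.** The commitment to report the other outcomes could be met by their T1 results alone, so the two sentences are in tension rather than in strict contradiction.
- **Late-acting outcomes.** It is tempting to add that several of these scales can change only after T1, which would make T2 the more informative reading. The documents do not support this. The objectives place all of these outcomes at T1. The rationale ties social support to the group format, discipline to reductions seen in the pilots, and knowledge to the CST strategies. Contact begins in week 2, so T1 falls about 18 − 2 = 16 weeks after first exposure. Food insecurity is the one arguable case, because its rationale is that "caregiving responsibilities often prevent caregivers from engaging in viable economic activities and lead to economic hardship". Even there the article does not say that change must come late. The point does not need this argument.
- **Protection elsewhere.** Persistence is tested on the CBCL and PEDsQL at T2, all eight scales are committed at T1, and the T2 analyses are openly labelled exploratory. This stands and limits the severity.

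**Conclusion.** The point holds in a limited form. The article itself makes T2 reporting of eight measured scales optional, with no criterion, decision time or alternative outlet. This is a stated rule, not a detail left to the SAP. It sits badly with the general reporting commitment and with the firm commitment to the exploratory moderation analyses in the same section. Followed as written, it permits selective reporting of exploratory results at the last randomised comparison.

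The conclusion that the choice could be made with estimates in view rests on two assumptions: that the secondary models keep the joint T1 and T2 structure, and that nothing fixes the choice before unmasking. The illustrative percentages rest further on the assumed alpha and correlations.

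Severity is low to moderate. The co-primary results at T1, the main secondary results at T2 and the secondary results at T1 are not touched, nor are sample size, power or alpha.

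**What to change.** In Outcomes {12}, replace the optional clause with: *T2 estimates and 95% confidence intervals for all eight will be reported together, labelled exploratory, in the main paper or its supplement, whatever the result.* The SAP should carry the same sentence before the trial statistician is unmasked.

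This moves the number of scales reported at T2 from anywhere between 0 and 8 to 8 of 8. It does not lower the chance of a nominally significant result among the eight, but it lets the reader see such a result beside the other seven.

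The cost is one supplementary table and the loss of discretion over space. No new data are needed, and no new models if the secondary models keep the arm-by-time term.

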### Participant timeline {13}

See Appendix Table 2.

### Sample size {14}

Each study cluster comprises 7 to 10 families. In intervention clusters, these families will all participate in the same CST group (with control clusters offered the intervention after data collection has been completed). Following WHO’s recommendations, CST groups will have a maximum of 10 caregivers. We anticipate having higher recruitment rates in the urban areas (i.e. 10 caregivers per cluster) compared to the rural areas (i.e. 7 caregivers per cluster), with an overall anticipated average cluster size of 8.5 caregivers.

Using a simulation and non-central chi-square approach [45], we determined that 14 clusters at each site (*n* = 476 caregivers in total) provided 96% (if effect size = 0.4) and 83% (if effect size = 0.32) power to detect the intervention effect for each co-primary at T1. The method accounted for (1) the cluster design, (2) the two co-primaries using a Bonferroni correction (i.e. alpha = 0.025), (3) realistic patterns of drop-out over repeated measures (i.e. 10% each at post-intervention and follow-up), (4) a missingness at random assumption, (5) pilot-test informed (i.e. 0.4) and conservative effect sizes (i.e. 0.32), and (6) intra-class correlation of 0.05 in our intervention arms. The random effects analysis model also co-varied for baseline and the country/site strata, and allowed for different group random effect variances for intervention and control arms, and different effects at T1 and T2 (i.e. including an intervention arm by time point interaction term in the model, with the effect at T1 extracted as the primary outcome). Furthermore, as this is a psychosocial trial with potential contamination concerns, we increased the number of trial clusters to 16 instead of 14 per site, bringing the total sample size to approximately 544 (i.e. an average of 8.5 families per cluster in 64 clusters) (Table 1).

**Table 1 Tab1:** Ethics approval information from collaborating institutions

Country	Name of ethics committee and/or governing body	Reference number	Status
UK	Health Faculties (purple) Research Ethics Subcommittee-King’s College London	RESCM-23/24–33742	Approved
Ethiopia	Scientific and Ethics Review Committee-Centre for Innovative Development and Therapeutic Trials for Africa (CDT Africa)	CDT/5564/22	Approved
	Institutional Review Board (IRB)-Addis Ababa University College of Health Sciences	AAYMF 03–008	Approved
Kenya	Institutional Scientific and Ethics Review Committee (ISERC)-Aga Khan University, Nairobi	2021/IERC-99 (V4, 26-Feb-2024)	Approved
	Kenya Medical Research Institute Scientific and Ethics Review Unit (SERU)	KEMRI/SERU/CGMR-C/272/4872 (V1.3, 26-Jan-24)	Approved
	National Commission for Science, Technology and Innovation (NACOSTI), Kenya	NACOSTI/P/24/33550	Approved

### Recruitment {15}

The primary recruitment strategy will be to use a community-based identification tool, developed by our research team and implemented by trained community support workers in the local communities, to select children identified as potentially having developmental disabilities. Awareness-raising training with community stakeholders (e.g. local leaders, religious leaders) will also be conducted in an effort to reduce stigma and create an enabling environment for the identification and engagement of children with DDs and their families. Identified children will be referred to health or education workers trained using principles from WHO’s mhGAP [22] for further assessment. Two- to nine-year-old children with a positive assessment (i.e. probable DD based on mhGAP assessment) will be referred to a specialist clinician (e.g. psychiatrist or clinical officers with specialist training) for a more comprehensive assessment to confirm or negate the diagnosis. Subsequently, the caregivers of children with a confirmed DD diagnosis will be contacted by our research assistants to assess their eligibility based on all inclusion and exclusion criteria and obtain consent if they are eligible and willing to participate in the trial.

If needed, to achieve our desired sample size, we will also recruit eligible participants from educational institutions, health centres, specialist clinics, and Kenyan Education Assessment and Resource Centres. Administrators of these centres, who are gatekeepers to the participants, will share information about the study with families living in the SPARK clusters with a 2–9-year old child suspected of having a DD to assess preliminary interest. Interested potential participants will be contacted by members of our research team to provide a referral for a formal diagnostic assessment if they are recruited from non-specialist health centres or educational institutions and lack a formal diagnosis. Upon receiving a formal diagnosis, they will be contacted again by our research team to assess their eligibility based on all inclusion and exclusion criteria and obtain consent if willing and eligible. Non-eligible families from either route will be referred to local health centres and provided with a resource kit containing information about relevant local resources and services in their areas.

## Assignment of interventions: allocation

### Sequence generation {16a}

We will use the bespoke randomisation system maintained by the King’s Clinical Trial Unit (KCTU) at King’s College London’s to design a web-based randomisation system for participant allocation. Clusters will be randomised in randomly permuted blocks of size two, stratified by site (Addis Ababa, Gurage/Silte, Nairobi, and Kilifi). The system will require a minimum of two clusters to be randomised within a given site at a time, to maintain allocation concealment. In extreme circumstances where, after all conceivable efforts to recruit have been exhausted, we only have a single cluster to randomise within a site, we will generate a dummy cluster that will be entered into the randomisation system to permit random allocation of the single cluster.

### Concealment mechanism {16b}

Country-specific authorised staff (data managers independent from the SPARK research or clinical teams) will conduct randomisation using KCTU’s online randomisation system. The co-principal investigator (co-PI) or delegate (e.g. trial manager) will request non-shareable, user-specific usernames and passwords from the KCTU for authorised staff to access the system. Authorised staff will randomise clusters by going to www.ctu.co.uk and clicking on the link to access the randomisation system. Site-specific cluster numbers will be entered into the randomisation system. The system maintains a full audit trail of all data entered, including the staff who entered the data and a timestamp of the entry. As per ‘Sequence generation {16a}’ section, clusters will be randomised in pairs to conceal allocations.

